## Abstract

**Background:**

Urinary tract infections (UTIs) are amongst the most common bacterial infections affecting women. Although antibiotics are the treatment of choice for UTI, cranberry derived products have been used for many years to prevent UTIs, with limited evidence as to their efficacy. Our objective is to assess the efficacy of a cranberry extract capsule standardized in A-type linkage proanthocyanidins (PACs) for the prevention of recurrent urinary tract infection.

**Methods:**

We will perform a 1:1 randomized, controlled, double blind clinical trial in women aged 18 years or more who present ≥2 UTIs in 6 months or ≥ 3 UTIs in 12 months. One hundred and forty-eight women will be recruited and randomized in two groups to either receive an optimal dose of cranberry extract quantified and standardized in PACs (2 × 18.5 mg PACs per day) or a control dose (2 × 1 mg PACs per day). The primary outcome for the trial is the mean number of new symptomatic UTIs in women during a 6-month intervention period. Secondary outcomes are: (1) To evaluate the mean number of new symptomatic UTIs with pyuria as demonstrated by a positive leucocyte esterase test; (2) To detect the mean number of new symptomatic culture-confirmed UTIs; (3) To quantify urinary PACs metabolites in women who take a daily dose of 37 mg PACs per day compared to women who take a daily dose of 2 mg per day for 6 months; (4) To characterize women who present recurrent UTI based on known risk factors for recurrent UTI; (5) To describe the side effects of daily intake of cranberry extract containing 37 mg PACs compared to 2 mg PACs. This report provides comprehensive methodological data for this randomized controlled trial.

**Discussion:**

The results of this trial will inform urologists, gynaecologists, family physicians and other healthcare professionals caring for healthy women with recurrent UTI, as to the benefits of daily use of an optimal dose of cranberry extract for the prevention of recurrent UTI.

**Trial registration:**

Clinicaltrials.gov, identifier: NCT02572895 October 8th 2015.

## Background

Urinary tract infections (UTIs) are one of the most common bacterial infections affecting women [1, 2]. UTI preferentially affects young, sexually active women with 50–60% of women reporting at least one UTI during their lifetime [2]. Nearly 1 in 3 women will experience at least one episode of UTI requiring antibiotic therapy before the age of 24 years and a quarter of these women will present reoccurrence within 6 months [1]^.^ Anatomical differences in male and female perineal anatomy may explain why women are more susceptible than men to the ascension of faecal bacteria in the urinary tract. More precisely, these anatomical features include a relative shortness of the urethra [3], the urethral meatus’s proximity to the anus and a more humid surrounding environment comparatively to the male anatomy [4, 5]. Additional well-established risk factors include spermicide-based contraception, history of previous UTI, first UTI before 15 years of age and those with UTI history in the mother [6–10].

Recurrent UTIs (r-UTI) are defined as more than 2 episodes in the last 6 months or 3 episodes in the last year [11]. The major symptoms of UTI include dysuria, increased frequency of urine, cloudy urine and occasionally hematuria [12]. In general, uncomplicated UTIs are confined to the bladder, resolve quickly following antibiotic treatment and thus are associated with fewer severe or long-term sequelae [13]. Though viewed as a benign affliction, uncomplicated lower UTI symptoms can have considerable impacts on the patient’s productivity and quality of life. A study of university women reported that patients suffering from UTI experienced 2.4 days of restricted activity, 1.2 days of lost time and 0.4 bed bound days due to their symptoms [7]. Presently, the Canadian Urological Association and Society of Obstetricians and Gynecologists of Canada recommendations for the treatment of uncomplicated r-UTI use one of three antibiotic treatment regimens: continuous antibiotic prophylaxis, post-coital antibiotic prophylaxis or self-start antibiotic therapy [11, 12]. Empirical and preventive antibiotics for the treatment of r-UTI have been established as the most cost-effective way to manage these infections. However, prescribing without confirmation of diagnosis and isolation of causal bacterial contributes to the growing problem of uropathogen resistance in primary care [14].

Cranberries have been used for numerous years to prevent UTIs. Research suggests that proanthocyanidins (PACs), a component of cranberries, inhibit the adherence of p-fimbriated *Escherichia coli* on uroepithelial cells of the bladder, preventing the adherence of bacteria to the mucosal surface of the urinary tract and thereby inhibiting bacterial proliferation [15]. A multicentre randomized clinical trial (RCT) in sexually active adult women showed that a daily dose of 36 mg PACs or more provided an optimal antibacterial effect in the urine [16]. A Cochrane systematic review published in 2012, could not definitively conclude on the efficacy of cranberry products for the prevention of r-UTI mainly because of a lack of observance to the intake of cranberry supplements in juice form and also because of varying PACs concentrations in the different clinical trials that were rarely quantified or standardized [17]. A systematic review in 2013 including trials conducted in women with r-UTI found a significantly decreased risk of UTI among women receiving cranberry-containing products compared to control (2 trials, Risk ratio (RR) = 0.53, 95%CI 0.33–0.83, I^2^ = 0%) [18].

Since these reviews, several well-designed trials have evaluated the effects of daily cranberry capsules in women with r-UTI. Most notably, an RCT compared the preventive effects of a cranberry juice (UR65) containing 40 mg PACs versus placebo on the relapse of UTI in women aged 20–79 years presenting acute complicated or uncomplicated cystitis with a history of r-UTI during a six-month follow-up [19] The authors found no significant difference in the relapse rates of UTI between groups (log-rank test, *p* = 0.4209). Similarly, a double blind RCT evaluated the effects of a daily dose of 500 mg of a commercial cranberry fruit powder (2 mg PACs) compared to a placebo in 176 women who experienced at least 2 symptomatic UTI in the twelve months preceding the study [20]. In this trial, the proportion of women who experienced greater than one UTI in the cranberry powder group was significantly lower than in the placebo group during the six-month follow-up period (10.8% vs 25.8%, *p* = 0.04). Although well designed, these studies presented several methodological flaws such as the inclusion of women with complicated UTIs related to catheterization in the former as well as the use of a sub-optimal dose of cranberries in the latter.

We hypothesize that the efficacy of cranberry products for the prevention of R-UTI in women will be strongly increased by the usage of an optimal dose of cranberry extracts in capsule form (standardized to 37 mg PACs per day) and by an adequate measure of participant observance.

## Methods

### Study design and objectives

To assess the effects of a standardized cranberry extract in sexually active healthy women who present r-UTI, we will undertake a double blind, prospective RCT with 2 arms comparing the mean number of new UTIs during a 6-month period after consumption of a standardized cranberry extract containing 37 mg PACs (2 × 18.5 mg PACs per day) with a control dose of 2 mg PACs (2 × 1 mg PACs per day) in women presenting r-UTI. This protocol was developed in accordance with the Standard Protocol Items: Recommendations for Interventional Trials (SPIRIT) Statement. The SPIRIT figure is illustrated in Fig. 1.

**Fig. 1 Fig1:**
[figure not shown]
Study procedures and characteristics of study visits

The primary objective is to evaluate, in sexually active women who present r-UTIs, the effects of a standardized cranberry extract containing 37 mg type-A linkage PACs per day, compared to a control dose of 2 mg PACs per day during a 6-month period on the incidence rate of newly symptomatic UTIs during a 6-month follow-up period. Secondary objectives are: (1) To evaluate the mean number of new symptomatic UTIs with pyuria as demonstrated by a positive leucocyte esterase test; (2) To detect the mean number of new symptomatic culture-confirmed UTIs; (3) To quantify urinary PACs metabolites in women who take a daily dose of 37 mg PACs per day compared to women who take a daily dose of 2 mg per day for 6 months; (4) To characterize women who present r-UTI based on known risk factors such as spermicidal contraception use, frequency of sexual relations, personal and familial history of UTI; (5) To describe the side effects of daily intake of cranberry extract containing 37 mg PACs compared to 2 mg PACs.

### Study participants and recruitment

This clinical trial aims to enrol sexually active non-pregnant non-lactating women aged 18 years and over presenting culture-confirmed r-UTI (defined as ≥2 UTIs in the past 6 months or ≥ 3 UTIs in the past 12 months). Women will be recruited in the Laval University community in Quebec City, Canada, through list serves and local clinician referrals as well as posters in medical clinics, social media, paid advertising and word of mouth. Women wishing to participate will contact the study coordinator who will explain the research project to them and verify eligibility according to inclusion and exclusion criteria (Table 1). The risks and benefits of the study will be thoroughly discussed and the consent form will be signed at the first of three visits at the Institute on Nutrition and Functional Foods (INAF).

**Table 1 Tab1:** Admissibility criteria for the cranberry extract for prevention of recurrent urinary tract infections trial

Inclusion Criteria	
Sexually active healthy women	
Aged 18 years and older	
Recent history of recurrent urinary tract infections (UTIs)^a^	
≥ 2 UTIs in the past 6 months and/or	
≥ 3 UTIs in the past 12 months	
No consumption of cranberry juice, polyphenol or antioxidant supplements in the last 2 weeks	
Exclusion Criteria	
Pregnancy	
History of anatomical urogenital anomalies, urogenital tract surgery	
History of acute or chronic renal failure, nephrolithiasis	
History of intestinal diseases causing malabsorption	
Anticoagulant medication in the last month	
Known allergy or intolerance to cranberry	

^a^UTIs diagnosed by a clinician and treated with antibiotic therapy

Potential participants will need to restrain exposure to systemic antimicrobial agents or cranberry derivatives in the two weeks preceding enrolment. Women with anatomical abnormalities of the urinary tract, a history of renal disease (renal failure, nephrolithiasis) or intestinal disease causing malabsorption (Crohn’s disease, Celiac disease), or anticoagulant therapy will be excluded. Furthermore, we will exclude women with known allergy or intolerance to cranberries.

#### Study randomization

Concealed randomization will be generated using computer aided block randomization by blocks of 10. Eligible women will be assigned 1:1 to consume a cranberry extract either formulated in high PAC content capsules (2 capsules of 18.5 mg PAC per day) or low PAC content capsules (2 capsules of 1 mg PAC per day) for 6 months. The low PAC content cranberry capsule is comparable to the majority of cranberry extract products presently approved by Health Canada [21] . The standardized capsules will be manufactured and provided by Diana Foods and will be distributed in opaque packaging in order to conceal colour variations from the research team. The PAC content of each cranberry treatment will be validated at INAF according to the standardized BL-DMAC method, using A2 procyanidin dimer as standard for the quantification [22]. All clinical investigation, laboratory analysis, data collection and assessment will be blinded to the randomization allocation.

#### Clinical follow-up

Each visit (0, 12 and 24 weeks) will include a short questionnaire documenting socio-demographic characteristics (*T* = 0 only), medication and natural health product intake, quality of life (SF-12) [23], risk factors for UTIs, and a validated food frequency questionnaire (FFQ) [24] modified for our study to specifically include foods containing PACs. Double data entry will be performed under the study coordinator supervision in order to promote data quality. Participants will be instructed to obtain a midstream urine sample according to standard methods suggested by the microbiological laboratory. A dipstick urinalysis using Chemstrip 9 (Roche Diagnostics USA) and a pregnancy test (ß-hCG) will be completed. Three 10 ml tubes will be placed in a − 80 °C freezer for urinary PAC metabolites measurements by ultra-high performance liquid chromatography coupled with mass spectrometry, and the urine sample for culture will be refrigerated and transported to the microbiology laboratory at the CHU de Quebec – Universite Laval within 24 h after collection.

During their participation, the women will be asked to contact the study coordinator if they present symptoms of UTI in order to schedule a visit at INAF to confirm the diagnosis by urinalysis and urine culture and to receive an appropriate antibiotic prescription based on their medical history and allergies. Women unable to present themselves at INAF will be prescribed antibiotics waiving a confirmation of their UTI. Women wishing to discontinue the consumption of capsules will be asked to present themselves at the 3 and 6-month visit in order to complete intention to treat analysis. The participants will be asked not to consume other products containing cranberry derivatives for the duration of the study and to consume their cranberry extracts 2–4 h preceding each visit. Participants will also be asked to limit intense physical activity for 24 h preceding each visit. After 24 weeks of participation, women will be provided with the option of prolonging their participation for an additional 24 weeks, with follow-up visits at 36 and 48 weeks. This data will provide information on seasonal variations in the incidence of UTI.

#### Sample size and statistical analysis

Statistical analyses will be performed using SAS 9.2 (SAS Institute Inc., USA). All analyses will be based on the intention-to-treat principle before unmasking the treatment groups. The baseline characteristics of both groups will be compared using a Student’s t test for continuous variables and a generalized linear model for nominal variables. The Poisson regression model, which allows us to adjust for participants that were lost to follow up, will be used to compare the incidence of UTI during the 6-month follow up period as well as side effects of the treatment. Subgroup analyses will be performed in order to evaluate the impact of cranberry capsules in pre- and post-menopausal women as well as women with certain risk factors for complicated UTI such as pelvic floor disorders and diabetes.

Based on the literature [17], we estimate that 35% of patients in the control group will present at least one UTI during the 6-month follow-up period. In total, 126 women will need to be recruited in order to detect a clinically significant difference of 25% between the 2 groups (10% of women assigned to the experimental group will have at least 1 UTI with a power of 80%). Based on our past clinical trial experience [25], we estimate that 15% of randomized participants will be lost to follow up, therefore 148 women will need to be recruited in order to have at least 126 participants who will complete the 24-week intervention.

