## End points

### Incidence of UTI

The primary endpoint is the average number of symptomatic UTIs during the 6-month follow-up period. Individuals with acute urinary symptoms such as pollakiuria, urgency, burning, suprapubic pain, and hematuria will be assessed by study staff and will have to provide a urine sample for urinalysis. Women who present both symptom and pyuria criteria, defined as a positive leukocyte esterase dipstick result, will be diagnosed as having confirmed symptomatic UTI and prescribed appropriate antibiotic treatment. If the urine culture results are positive, the episode will be categorized as a culture-confirmed UTI. Women with symptomatic UTI during the study period will continue to take the cranberry capsules and remain in the study for the full 6 months unless they are lost to follow up or discontinue the intervention.

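### The primary Poisson comparison names no baseline covariate and baseline differences are tested for significance, although prior UTI is a named risk factor; pre-specified adjustment would bring a modest gain in precision

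*Protocol article*

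**What the plan says.** All references are to the protocol article.

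- **Baseline comparison** (Sample size and statistical analysis): "The baseline characteristics of both groups will be compared using a" Student's t test if continuous, or a generalized linear model if nominal. No use of the result is stated.
- **Primary endpoint** (End points, Incidence of UTI): "The primary endpoint is the average number of symptomatic UTIs during the 6-month follow-up period".
- **Primary model** (Sample size and statistical analysis): "The Poisson regression model, which allows us to adjust for participants that were lost to follow up" is to compare incidence over the 6 months. No baseline covariate is named.
- **Randomization** (Study randomization): 1:1 in blocks of 10, with no stratification factor named.
- **Prior UTI as a risk factor** (Background): "Additional well-established risk factors include spermicide-based contraception, history of previous UTI", among others. No effect size is given.
- **Prior UTI at entry** (Table 1): "Recent history of recurrent urinary tract infections", met by at least 2 "UTIs in the past 6 months and/or" at least 3 in the past 12 months. A footnote limits this to clinician-diagnosed, antibiotic-treated episodes.
- **Prior UTI as a baseline item**: secondary objective 4 is to characterize the women on risk factors that include "personal and familial history of UTI", and the questionnaire at weeks 0, 12 and 24 covers UTI risk factors (Clinical follow-up).

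**The concern.** Two things stand out when these places are read together.

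First, allocation is random and concealed, so any baseline difference between the arms arises by chance. A test of that difference addresses a null hypothesis already known to be true. At any level alpha, a fraction alpha of such tests is expected to be significant by chance, and a non-significant result does not show that an imbalance is harmless. What matters is how strongly the variable predicts the outcome, and the test does not measure that.

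Second, a woman's past UTI frequency is a natural predictor of a recurrent-event count, and the article itself calls it a risk factor. As described, neither the randomization nor the primary model uses it. Variation in UTI counts that prior frequency could explain therefore stays in the standard error of the rate ratio. What is at stake is precision, hence power and the width of the confidence interval.

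**Working it through.** **Inputs from the article.** 126 evaluable women (63 per arm); 35% of controls with at least one UTI in 6 months; Poisson regression of a 6-month count.

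**The plan's own figures.** The article gives no figure for the value of adjustment, so there is none to reproduce on this point. The 126 is used only as the size of the simulated trial. For 35% versus 10% at 80% power and two-sided alpha 0.05 (alpha is not stated), the usual two-proportion formula gives 43 per arm, 86 in total, so 126 does not follow from those inputs. The dropout step agrees up to rounding: 126/0.85 = 148.2, against 148 stated. That is a separate matter, and nothing below depends on it.

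**Assumptions, because the documents are silent.** True rate ratio 0.5; gamma overdispersion 0.5; prior UTIs above the entry threshold distributed as Poisson with mean 1.5, capped at 6; equal follow-up; two-sided 5% test with robust standard errors. The control mean is either -ln(1 - 0.35) = 0.43 UTIs, the Poisson mean matching 35% with at least one event, or 1.0. Each additional prior UTI multiplies the rate by 1.0 (no prediction), 1.2 or 1.4.

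**Calculation.** 1,500 trials per setting, each analysed with and without prior count. Monte Carlo error of a power figure is about sqrt(0.5 x 0.5/1500) = 1.3 points. Variance change = (SD adjusted / SD unadjusted)^2 - 1, where SD is the spread of the estimated log rate ratio.

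| Rate multiplier per prior UTI | Control mean | Power, unadjusted to adjusted | SD, unadjusted to adjusted | Variance change |
|---|---|---|---|---|
| 1.0 | 0.43 | 52.2 to 52.3% | 0.351 to 0.353 | +1% |
| 1.0 | 1.0 | 80.9 to 81.2% | 0.259 to 0.260 | +1% |
| 1.2 | 0.43 | 49.2 to 49.5% | 0.380 to 0.380 | 0% |
| 1.2 | 1.0 | 78.8 to 79.9% | 0.261 to 0.259 | -2% |
| 1.4 | 0.43 | 46.9 to 49.8% | 0.397 to 0.385 | -6% |
| 1.4 | 1.0 | 74.9 to 78.7% | 0.289 to 0.271 | -12% |

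Worked example, last row: (0.271/0.289)^2 = 0.879, a 12% lower variance and 3.8 points more power.

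**Type I error.** With a true rate ratio of 1, rejection rates across the settings were 4.4 to 7.5% unadjusted and 4.5 to 7.5% adjusted. The two models differed by at most 0.4 points in any one setting, so adjustment neither causes nor cures the excess over 5% seen in some settings.

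**Cross-check under other assumptions.** A smaller simulation (250 trials per setting, rate ratio 0.6, entry at 3 or more UTIs in 12 months) gave standard errors of 0.311 to 0.302, 0.228 to 0.217 and 0.254 to 0.241 for three degrees of heterogeneity. These are variance reductions of 6%, 9% and 10%. With |ln 0.6| = 0.511 and power approximately Phi(0.511/SE - 1.96):

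- SE 0.311 to 0.302: 38% to 39%
- SE 0.228 to 0.217: 61% to 65%
- SE 0.254 to 0.241: 52% to 56%

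These gains of about 2 to 4 points agree with the table. The raw rejection rates rose by more, in one setting from 51% to 61%. That exceeds what the standard errors imply, and each rate carries a Monte Carlo error of about 3 points, so the 10-point rise should not be relied on.

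**The case against.** The strongest reply is that a journal article condenses the full protocol, that the remark about loss to follow-up explains why Poisson regression was chosen rather than listing its terms, and that covariates may be named in a document not shown. This largely stands against one inference that a reader might draw, that the primary comparison is declared unadjusted. The article never says so. What can be said is that, as described, the model names no baseline covariate. The planned baseline tests, by contrast, are stated outright and are not a matter of omission.

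Three further objections also hold in part.

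- A reader might infer that baseline p-values will be used to handle imbalance or to select covariates. The article says only that the groups will be compared. Naming tests but no covariate leaves room for such selection; it does not show that selection is planned.
- A reader might infer that a 12-month count is on file for every woman. The entry criteria are thresholds joined by and/or, so a woman can qualify on the 6-month criterion alone, and no numeric count is stated as recorded. That the history is obtained at screening is clear. That the baseline questionnaire also covers it is a reasonable reading of its risk-factor section alongside secondary objective 4.
- A reader might take prior UTI count to be a strong predictor here. The Background lists "history of previous UTI, first UTI before 15 years of age" as risk factors for UTI in general. Every enrolled woman already meets the recurrence threshold, which narrows the range of the covariate and may weaken it.

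None of this removes the case for adjustment: it rests on the article's own choice of risk factor, and in the simulations a covariate with no predictive value cost essentially nothing.

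**Conclusion.** The point holds as one of efficiency and good practice. The baseline significance tests are uninformative, though dropping them changes no efficacy result. Pre-specifying prior UTI frequency in the primary model improves on the method described: about 0 to 12% lower variance and 0 to 4 points of power. This range depends on the assumed overdispersion, event rate, rate ratio and predictor strength, and the gain is essentially nil if prior count does not predict.

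It would be wrong to go on to call the planned comparison invalid. In a 1:1 randomized trial, leaving out a baseline covariate does not bias the treatment comparison, and chance imbalance is already reflected in a correctly estimated standard error. The simulated type I error was essentially the same with and without the covariate.

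**What to change.** Before unmasking:

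1. Pre-specify the primary Poisson model as treatment + prior UTI frequency as recorded at screening, with log follow-up time as offset. Use the 12-month count if it is available, otherwise the recorded 6- or 12-month entry history. Fix the coding and the handling of missing values in advance.
2. Keep the model without the covariate as a supportive analysis.
3. Replace the baseline t tests and generalized linear models with descriptive statistics by arm, without p-values.
4. If a fuller protocol or SAP already names the covariates, confirm that it does so; then only item 3 remains.

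**Cost.** A few sentences in the analysis section and no new measurement on participants, but the count or entry history has to be extracted from screening records and may be less complete than a purpose-collected variable. The return is small if prior frequency predicts weakly among women who all meet the recurrence threshold.

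### Poisson regression is fixed for a repeat-event UTI count with no provision for overdispersion, so the standard error of the rate ratio may be too small

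*Protocol article*

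**What the plan says.** Under *Incidence of UTI* the Protocol article defines the outcome as a count: "The primary endpoint is the average number of symptomatic UTIs during the 6-month follow-up period". Repeat episodes enter it: "Women with symptomatic UTI during the study period will continue to take the cranberry capsules and remain in the study for the full 6 months". The exceptions are women who drop out of follow-up or stop the capsules.

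Under *Sample size and statistical analysis* one model is named: "The Poisson regression model, which allows us to adjust for participants that were lost to follow up, will be used to compare the incidence". The comparison is of UTI over six months, and the same model is to serve for side effects. That section mentions no scale parameter, robust variance, negative binomial alternative, dispersion check or covariate.

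The article also describes a mixed population:
- *Background*: "Additional well-established risk factors include spermicide-based contraception, history of previous UTI, first UTI before 15 years of age", together with maternal history.
- The secondary objectives: "known risk factors such as spermicidal contraception use, frequency of sexual relations, personal and familial history of UTI".
- *Study participants and recruitment*: an entry history of "≥2 UTIs in the past 6 months or ≥ 3 UTIs in the past 12 months", with no upper limit.
- The planned subgroups: "pre- and post-menopausal women as well as women with certain risk factors for complicated UTI such as pelvic floor disorders and diabetes".

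The sample size rests on a yes/no proportion: "we estimate that 35% of patients in the control group will present at least one UTI during the 6-month follow-up period", against 10% in the experimental arm, with 80% power and 126 evaluable women.

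**The concern.** Model-based Poisson standard errors are valid only if, given the covariates in the model, the variance of the counts equals their mean. Women with different underlying rates, where the model does not carry the difference, produce counts with variance above the mean. An offset for follow-up time handles unequal exposure, which is the reason the article gives, but it leaves the extra variance untouched.

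This concerns the test that decides the trial. If the standard error is too small, the p-value is too small, the confidence interval for the rate ratio is too narrow, and a benefit could be declared that an analysis with the right variance would not support. The estimated rate ratio itself is not affected.

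**Working it through.** **Inputs from the Protocol article.** Control proportion with at least one UTI 0.35; experimental 0.10; power 80%; 126 evaluable women, so 63 per arm at 1:1; 15% loss.

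**Assumed.** Two-sided 5% level (the article states none). Gamma-distributed rates between women, giving variance μ + kμ². The range k = 0.25 to 2 is an assumption.

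**The plan's own figure.** With p̄ = 0.225, the usual two-proportion formula gives [1.96·√(2·0.225·0.775) + 0.842·√(0.35·0.65 + 0.10·0.90)]² / 0.25² = 42.6, so 43 per arm or 86 in total (102 with continuity correction). The stated 126 is not reproduced at this level. That is a separate matter; 63 per arm is used below as planned. The recruitment target follows: 126/0.85 = 148.2, stated as 148.

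**Size of the error.**
1. Choose μ so that 35% of women have at least one UTI: μ = −ln(0.65) = 0.431 for k = 0, otherwise μ = (0.65^(−k) − 1)/k.
2. The variance/mean ratio is 1 + kμ. The Poisson standard error is too small by a factor √(1 + kμ).
3. The approximate type I error is 2·[1 − Φ(1.96/√(1 + kμ))].
4. Check by simulation: 63 per arm, no treatment effect, 40,000 trials per row, Wald test of the log rate ratio.

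| k | μ | variance/mean | SE factor | type I error, formula | simulated, Poisson SE | simulated, Pearson-scaled | simulated, robust |
|---|---|---|---|---|---|---|---|
| 0 | 0.431 | 1.00 | 1.00 | 5.0% | 4.8% | 5.0% | 5.1% |
| 0.25 | 0.455 | 1.11 | 1.06 | 6.3% | 6.1% | 5.1% | 5.3% |
| 0.5 | 0.481 | 1.24 | 1.11 | 7.8% | 7.5% | 5.0% | 5.3% |
| 1 | 0.538 | 1.54 | 1.24 | 11.4% | 10.6% | 4.8% | 5.4% |
| 2 | 0.683 | 2.37 | 1.54 | 20.3% | 19.4% | 5.2% | 6.1% |

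Holding the mean at 0.43 instead gives 7.2%, 9.8% and 14.6% for k = 0.5, 1 and 2. Coverage of the nominal 95% interval is then 92.8%, 90.2% and 85.4%.

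**Effect of the entry rule.** Restricting entry to recurrent UTI removes low-rate women and so reduces the spread. When gamma-rate women are selected by the rule, the variance/mean ratio is about 1.2–1.7. Putting 1.2 and 1.7 into step 3 gives 7.4% and 13.3%. This range also depends on the rates assumed in the source population and is not tied to the 35%. One setting that nearly matches it (source mean 0.25 UTI per six months, k = 0.5) gave 36% with at least one UTI, a ratio of 1.11 and about 6%.

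**Power after the fix.** With means 0.431 and −ln(0.90) = 0.105, negative binomial n per arm = (1.96 + 0.842)²·(1/0.431 + 1/0.105 + 2k) / [ln(0.105/0.431)]². This gives 47, 51, 55 and 63 for k = 0, 0.5, 1 and 2, against 63 planned.

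**The case against.** The article names a model family. It does not say that the scale is fixed at 1, that standard errors are model-based or that the model is unadjusted. Poisson regression with robust or scaled errors would still fit its wording, and a statistical analysis plan that is not shown could choose the variance method. Risk factors are recorded at each visit and could enter the model; they show that crude rates differ, not how much variance would remain after adjustment. Each episode is treated and the entry rule removes low-rate women, and both could limit dispersion.

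Most of this stands, and it limits the claim to a conditional one. It does not remove the point: the article chooses and justifies a model for the primary comparison, and the justification does not cover the assumption most at risk with repeat events.

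A reader might go further in three ways that the documents do not support:
- **That the false-positive rate is certain to be well above 5%, even near 28%.** That figure needs a mean of 1.2 with k = 2, which implies 1 − 3.4^(−0.5) = 46% of women with a UTI, not the planned 35%. No dispersion is given anywhere.
- **That relapse after incomplete clearance adds clustering within a woman.** The article does not say so, and its *Background* describes uncomplicated infections as resolving quickly with antibiotics.
- **That side effects are worse affected.** The article does not say whether they are analysed as counts or as any/none. For a yes/no outcome, Poisson model-based errors are conservative.

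**Conclusion.** The point holds in conditional form. The direction follows from the model: unexplained differences in rate make the Poisson standard error too small, and the article itself gives reason to expect such differences. The size is not in the documents. Anchored to the planned 35%, it runs from slight (about 6% at k = 0.25) through material (about 7–11% at k = 0.5–1) to about 20% at k = 2. Selection by the entry rule points to about 7–13%, under its own assumptions. All figures assume gamma-distributed rates, a two-sided 5% level, 63 per arm and a model without covariates.

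It would be wrong to conclude that the primary test is invalid as planned or that the trial is too small for a corrected analysis. What is overstated is precision, and the planned size can absorb the correction at the planned effect.

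**What to change.** Before the groups are unmasked, state that the primary analysis is a negative binomial regression, or a Poisson regression with Pearson-scaled or robust standard errors, with log follow-up time as offset. Name one of these as primary. Ordinary Poisson regression can stay as a sensitivity analysis. Apply the same rule to side effects only where they are analysed as counts.

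In the simulations above, Pearson-scaled errors kept the type I error at 4.8–5.2% and robust errors at 5.1–6.1%; the negative binomial test was not simulated for type I error. All three options are available in SAS GENMOD.

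The cost is one sentence. If the counts are overdispersed the interval widens, by a factor of about 1.1–1.2 for k of 0.5–1 at the planned control rate; if they are not, it is practically unchanged.
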